### Statistical analysis

Patient characteristics will be summarized with descriptive statistics. Comparative analyses will be based on the full trial cohort, using the intention-to-treat (ITT) principle (i.e., based on the participant’s randomized allocation). Reasons for missing data will be examined, and appropriate imputation methods will be used to address missing follow-up data, retaining the entire cohort for the ITT analysis. Interim analyses will occur for primary outcome measure when 50% of recruited patients finish their 1-year follow-up. Using the O’Brien-Fleming criteria for sequential tests, the significance level will be 0.005 for the interim analysis and 0.049 for the final analysis. The O’Brien-Fleming boundaries, as well as clinical judgment concerning adverse events, will be used as guidelines for stopping the study early. However, this interim analysis will only occur if randomization is not yet complete.

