**Methods:**

We will conduct a prospective, single blind randomized controlled parallel arm trial to compare non-operative management of proximal humerus fractures with open reduction and internal fixation using locked plating technology. One-hundred and sixty patients > age 60 with acute 3- or 4- part proximal humerus fractures will be randomized to either open reduction and internal fixation with locked plating technology or non-operative management treatment arms. The primary outcome measure is the Constant Score at 24 months post-operative. Secondary outcome measures include the American Shoulder and Elbow Surgeon’s Score (ASES), EuroQol EQ-5D-5 L Health Questionnaire Score, short form PROMIS upper extremity score and IPAQ for the elderly score. Further outcome measures include assessment of the initial classification, displacement and angulation and the quality of surgical reduction via a standard computed tomography (CT) scan; rates of non-union, malunion, arthrosis, osteopenia or other complications including infection, nerve injury, intra-articular screw penetration, reoperation rates and hospital re-admission rates.

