### Sample size calculation

The sample size will be 160 patients. The minimum clinically important difference for the Constant score is 12 [52, 53], with standard deviation of 23.1 from measurements in previous studies of similar patient populations. For the primary outcome, to achieve 80% power to detect a clinically meaningful difference of 12 points on the Constant score, with standard deviation of 23.1, and alpha of 0.05, a sample size of approximately 116 people would be necessary (58 per arm). The overall sample size is increased from 116 to 129 to account for an expected 5% crossover from the non-operative study arm to the operative study arm. An additional 31 patients were added for a conservative sample size adjustment accounting for 20% loss-to-follow-up over the two years of follow-up, for a total sample size of 160 patients.

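### The interim efficacy look on the primary outcome is triggered at 1-year follow-up although that outcome is the 24-month Constant score, and 0.005/0.049 is not a matched O'Brien-Fleming pair

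*Protocol article*

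**What the plan says.** The Methods part of the abstract fixes the endpoint: "The primary outcome measure is the Constant Score at 24 months post-operative". The Primary objective analysis section agrees, since its ANOVA compares mean Constant scores at 2 years. Scores are also collected at baseline, 3, 6 and 12 months (Outcome measures), so a 12-month score exists but is not the primary time point.

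The Statistical analysis section then sets the interim: "Interim analyses will occur for primary outcome measure when 50% of recruited patients finish their 1-year follow-up". It invokes O'Brien-Fleming and gives the levels: "the significance level will be 0.005 for the interim analysis and 0.049 for the final analysis". The boundaries, "as well as clinical judgment concerning adverse events, will be used as guidelines for stopping the study early". The look is conditional: "this interim analysis will only occur if randomization is not yet complete".

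The overall alpha comes from the Sample size calculation section: "and alpha of 0.05, a sample size of approximately 116 people would be necessary (58 per arm". The article does not say which Constant score the interim tests, or how a 12-month result would enter the boundary.

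**The concern.** An O'Brien-Fleming boundary assumes that the same endpoint is tested at each look and that the information fraction is known. Here the trigger counts patients 12 months before the primary outcome is observed in them, so neither the endpoint nor the fraction is settled. There are two ways to read the rule, and the stated interim level fits neither.

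- **The look tests 12-month scores.** It is then not a look at the primary outcome, and its correlation with the final test is lower than the boundary assumes.
- **The look tests 24-month scores.** Only patients enrolled at least a further year earlier have them, so the fraction is well below one half and 0.005 is far too lenient for an O'Brien-Fleming rule.

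At stake is an early-stopping recommendation that does not bear on the 24-month question in the way its label implies. The two stated levels also do not belong together.

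**Working it through.** **Inputs.** From the article: alpha 0.05, power 80%, difference 12, SD 23.1, 58 per arm, total 160, 1:1 allocation, levels 0.005 and 0.049, trigger at 50% with 1-year follow-up. Assumed, because not stated: two-sided tests, trigger at 80 of 160 patients, uniform accrual over A years, no loss to follow-up, and a 12/24-month correlation rho.

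**Sample size as a check on sidedness.** n per arm = 2(1.960 + 0.842)² × 23.1²/12² = 58.2. This agrees with the article's approximate 58, so two-sided 0.05 is the right reading. An exact t-test calculation gives 59; power at 58 is 79.9%.

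**24-month information at the trigger.** The 80th patient enters at A/2 and completes 1 year at A/2 + 1. Patients with 24-month scores at that moment entered by A/2 − 1. Their fraction is t = (A/2 − 1)/A = 0.5 − 1/A.

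O'Brien-Fleming-type spending at t comes in two common forms: (i) 2[1 − Φ(1.960/√t)] and (ii) 4[1 − Φ(2.241/√t)].

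| A (years) | t | Patients with 24-month score | Form (i) | Form (ii) |
|---|---|---|---|---|
| 3 | 0.17 | 27 | 0.000002 | 0.00000008 |
| 4 | 0.25 | 40 | 0.00009 | 0.00001 |
| 5 | 0.30 | 48 | 0.00035 | 0.00009 |
| 8 | 0.375 | 60 | 0.0014 | 0.0005 |

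For 3 to 5 years the level is below about 0.0004. Even at 8 years it is well short of 0.005.

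**Overall alpha of the stated pair.** The critical values are 2.807 (0.005) and 1.969 (0.049). Overall alpha = 1 − P(|Z1| < 2.807, |Z2| < 1.969), with (Z1, Z2) bivariate normal. The correlation is √t for the same endpoint, and rho × √0.5 if the interim uses 12-month scores on half the patients.

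- Same endpoint, t = 0.5: 0.0509.
- Smallest values that round to the pair (0.0045/0.0485), t = 0.5: 0.0502, so rounding does not explain it.
- 12-month scores, rho = 0.7 (correlation 0.495): 0.0524.
- 12-month scores, rho = 0.5 (correlation 0.354): 0.0531.
- 24-month scores, A = 3, 4, 5: 0.0529, 0.0524, 0.0521.

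**Matched pairs at t = 0.5.** Classical O'Brien-Fleming (constant 1.977) gives 0.0052/0.0480. Spending form (ii) gives 0.0031/0.0490. Form (i) gives 0.0056/0.0478. The plan's interim level is close to the classical one and its final level is that of form (ii). As rounded pairs, 0.005/0.048 gives 0.0499 and 0.003/0.049 gives 0.0500. With 0.005 at the interim, the final level must be 0.0481. The stated pair holds 5% only from t of about 0.65 upwards.

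**Illustration of a stop on 12-month scores.** With 40 per arm and SD 23.1, the standard error is 23.1 × √(2/40) = 5.165. A true 12-month difference of 12 points gives 12/5.165 = 2.323, and the crossing probability is Φ(2.323 − 2.807) = 31%. For 8 points it is 10%, and for 4 points 2%.

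**The case against.** The strongest defence is that the look is modest. It happens only while randomization is open, its boundaries are guidelines used alongside clinical judgment on adverse events, and interim mechanics are often left to an analysis plan that is not shown here. The section on primary outcome measures also lists the Constant score without a time point, so a 12-month look may be what was meant. This lowers the severity. It does not remove the mismatch, because the article itself states the endpoint, the trigger and the levels, and they do not fit together.

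Some stronger readings are tempting but not supported:

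- **Material alpha inflation.** The excess is 0.09 percentage points at half information. The extreme of 0.0538 needs zero correlation between interim and final statistics, which is implausible for the same score in overlapping patients.
- **A final level of 0.049 is wrong if no interim is held.** It is only slightly conservative. The condition depends on recruitment and not on outcome data, and power at 58 per arm is 79.6% instead of 79.9%.
- **No 24-month data at all at the look.** The formula gives t = 0 at A = 2, but the trigger then falls at year 2, when recruitment ends, and the plan's own condition cancels the look.
- **A fixed ceiling of 0.00009 for the interim level.** That is form (ii) at A = 5 only. Form (i), or longer accrual, gives more.
- **The trial will stop on a transient effect and leave its question unanswered.** The 31% and 10% suppose a 12-month difference that vanishes by 24 months. No passage supports that course; the Background cites two randomized trials with no significant functional difference over 2 years. Nor does the article say that follow-up of enrolled patients would cease after a stop.

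**Conclusion.** The concern holds as a should-fix. The main defect is the contradiction between a 1-year trigger and a 24-month primary outcome. Either the endpoint at the look is not the primary one, or the look rests on roughly 0.17 to 0.30 of the 24-month information (uniform accrual over 3 to 5 years, an assumption), where an O'Brien-Fleming-type level is below about 0.0004. The mismatched pair is a minor numerical error: 0.0509 at half information, and about 0.052 to 0.053 with 12-month scores at an assumed correlation of 0.5 to 0.7. It matters only if the look is held. The crossing probabilities are illustrative and do not carry the conclusion.

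**What to change.** State which Constant score the interim tests, and match the rule to it in one of two ways.

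1. Make the 1-year look a safety review with no efficacy stop, and test the final analysis at 0.05.
2. Allow an efficacy stop only on 24-month Constant scores, with a named spending function evaluated at the actual fraction of 24-month data.

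If a look at 50% of 24-month data is kept under the second option, use 0.005/0.048 or 0.003/0.049. Reconcile its timing with the condition that randomization is still open: under uniform accrual it falls at A/2 + 2 years, which lies within recruitment only if A exceeds 4.

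The change is one of wording and thresholds. Sample size is essentially unaffected: power at 58 per arm is 79.9% at 0.05 and 79.4% at 0.048. The real cost is that an early efficacy stop is lost under the first option and delayed under the second.

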### Primary objective analysis

A.The analysis involves a comparison of the mean Constant scores between the two groups on an intention-to-treat basis. An ANOVA will be used to assess whether there is a statistically significant difference between treatment groups for the mean Constant scores at 2 years, with stratification factor included. A non-parametric Kruskal-Wallis will be instead used if parametric tests are not justified. In addition, a Generalized Estimated Equations (GEE) analysis will be conducted to determine whether there is an effect over time (repeated measures) (i.e. pre-operatively, 3, 6, 12 and 24 months follow-ups).

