### Participants

Patients will be screened in the emergency department of a large University-affiliated hospital and will be enrolled in the fracture clinic. Table 1 lists eligibility criteria for the study. Enrolled patients include males and females > age 60 with acute (< 3 weeks) displaced proximal humerus fractures that fall into the Neer category of 3- or 4- part. Diagnosis will be obtained from radiographs including a true AP (neutral rotation) of the shoulder, a lateral Y-view and an axillary (or trauma axillary) view. The fractures reviewed for inclusion will be independently assessed by two Orthopaedic Surgeons participating in the trial. If there is any disagreement on the classification or inclusion, a third surgeon will be asked to review. The majority consensus will be the implemented inclusion and classification. Eligible patients that have consented to participate in the study will receive informed consent on the two treatment arms prior to randomization. Preoperative baseline functional assessment including the Constant, ASES, EQ-5D-5 L, PROMIS and IPAQ scores will be completed. Patients randomized to the surgical arm will undergo surgery within 7 days of presentation.

**Table 1 Tab1:** Inclusion and Exclusion Criteria

Inclusion Criteria	
1. Displaced 3-part proximal humerus fractures by the Neer classification; or displaced 4-part proximal humeral fractures by the Neer classification that are deemed amenable to surgical internal fixation	
2. > 60 years of age	
3. Low energy mechanism of injury	
4. Acute fracture^a^	
Exclusion Criteria	
1. 4-part proximal humerus fractures that are not deemed amenable to surgical fixation^b^; fractures that are better suited to treatment with arthroplasty	
2. Isolated greater tuberosity fractures	
3. Ipsilateral upper extremity significant injury, concomitant fracture or polytrauma	
4. Open fracture	
5. Previous ipsilateral shoulder surgery	
6. Patients with active worker’s compensation claims^c^	
7. Active joint or systemic infection	
8. Patients with convulsive disorders, collagen diseases, and any other conditions that might affect the mobility of the shoulder joint	
9. Major medical illness^d^	
10. Unable to speak or read English/French	
11. Psychiatric illness that precludes informed consent	
12. Unwilling to be followed for 2 years	

^a^ <3 weeks

^b^due to osteopenic bone, thin head or tuberosity fragments

^c^due to the expectation of lower rates of success in this patient population

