### Outcome measures

Outcome measures are separated into primary and secondary as outlines below. All functional assessment scores will be completed at baseline and 3, 6, 12 and 24 months post injury. Complications and adverse events will be recorded on standardized case-report forms that will be completed immediately following the completion of the surgical procedure for patients randomized to the surgical treatment arm. At follow-up visits, clinical evaluation will be conducted to monitor for complications including infection, nerve injury, and hematoma formation or hospital re-admission.

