### Secondary objective analysis

A.ANOVAs will be used to compare the following two-year outcome measures between the two groups: ASES, EQ-5D-5 L, PROMIS and IPAQ. In addition, the incidence proportion of complications will be derived for each group, and a comparison of the two groups will be conducted for re-operation, infection, nerve injury, hematoma, hospital readmission, and intra-articular screw penetration using a chi-square analysis. Logistic regression modeling will be used to account for variables demonstrating group imbalance.B.The incidence of malunion, non-union, and osteoarthritis will be compared between groups using chi-square statistics (and odds ratios). Time to union will be determined with Kaplan-Meier curves with a log rank test for group comparisons.C.The degree of association between the degree of displacement and angulation of the fracture fragments and the Constant score will be determined. Multivariable regression analysis will be carried out to determine if an association exists between fracture angle and the degree of displacement (independent variables), and functional outcomes using the Constant score (dependent variable). If such an association is identified, area under the curve plots will be used to determine at what degree of angulation or displacement a particular treatment is indicated.D.The degree of association between the quality of surgical reduction [degree of displacement/angulation] of the fragments based on post-operative CT scan and the Constant functional outcome measure will be determined in the surgical group using a multivariable regression analysis.

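### The primary ANOVA leaves out the baseline Constant score the trial collects, and its Kruskal-Wallis fallback drops the randomisation stratum and the mean difference

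*Protocol article*

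**What the plan says.** Under Primary objective analysis, the protocol article specifies an ANOVA for the "difference between treatment groups for the mean Constant scores at 2 years, with stratification factor included". The stratification factor is fracture type, 3-part or 4-part (Randomization and blinding). No other covariate is named. The next sentence provides a replacement test: "A non-parametric Kruskal-Wallis will be instead used if parametric tests are not justified". It does not say what would make parametric tests unjustified.

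A GEE is added to the ANOVA: "analysis will be conducted to determine whether there is an effect over time (repeated measures". Its time points are given as "pre-operatively, 3, 6, 12 and 24 months follow-ups".

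Under Secondary objective analysis, "ANOVAs will be used to compare the following two-year outcome measures between the two groups", namely ASES, EQ-5D-5L, PROMIS and IPAQ. Neither baseline nor stratum is mentioned there.

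Every one of these scores has a baseline value. Participants states: "Preoperative baseline functional assessment including the Constant, ASES, EQ-5D-5 L, PROMIS and IPAQ scores will be completed". Outcome measures confirms it: "All functional assessment scores will be completed at baseline and 3, 6, 12 and 24 months post injury".

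**The concern.** There are two points of substance and one of wording.

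**Baseline.** A pre-treatment measurement of the outcome is often a useful covariate in a two-arm comparison of means. The trial pays to collect it, then leaves it out of the model that decides the primary question. What is lost is precision, in a trial whose power sits just under 80% once its own crossover and loss allowances are applied.

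**Fallback.** The Kruskal-Wallis test would replace the primary test; it is not offered as a sensitivity analysis. With two arms it is the unstratified rank-sum test. It therefore drops the factor used in randomisation, which the preceding sentence of the plan includes. It also yields no difference in mean scores, although the section defines the analysis as a comparison of means and the sample size rests on 12 points. The protocol hypothesises no significant difference (Purpose and hypothesis). If that is the result, a confidence interval for the mean difference shows whether 12 points is excluded, and a rank-test p-value does not. Because the trigger is undefined, the choice of primary test can follow the data.

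**GEE.** The stated aim names no treatment or treatment-by-visit term, so the quantity to be reported is unclear.

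**Working it through.** **1. The plan's own sample size.** Inputs from Sample size calculation: difference 12, SD 23.1, alpha 0.05 (taken as two-sided), power 80%.

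- Per arm: 2 × [23.1 × (1.960 + 0.842) / 12]² = 58.2. The protocol states 58 per arm, 116 in total.
- Crossover of 5%: 116 / 0.95² = 128.5, rounded to 129, as stated.
- Loss of 20%: 129 / 0.8 = 161.25, against 160 stated. This is close enough.

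The figures reproduce. The calculation is an unadjusted two-sample one with no baseline correlation.

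**2. Power with and without baseline.** Inputs:

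- Evaluable patients: 160 × 0.8 = 128, or 64 per arm.
- Effect after 5% crossover under intention to treat: 12 × 0.95 = 11.4.
- Final alpha: 0.049 (Statistical analysis).
- Baseline-to-24-month correlation r: not in the document, so assumed and shown as a range.

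Formula: residual SD = 23.1 × √(1 − r²); noncentrality = 11.4 / (SD × √(2/64)); power from the noncentral t distribution with 126 degrees of freedom.

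| r (assumed) | Residual SD | Noncentrality | Power |
|---|---|---|---|
| 0 (no baseline) | 23.10 | 2.79 | 78.9% |
| 0.1 | 22.98 | 2.81 | 79.3% |
| 0.2 | 22.63 | 2.85 | 80.5% |
| 0.3 | 22.04 | 2.93 | 82.5% |
| 0.4 | 21.17 | 3.05 | 85.4% |
| 0.5 | 20.01 | 3.22 | 89.1% |

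The planned ANOVA already contains the stratum, so r is best read as the correlation within fracture type.

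**3. Cost of the fallback.** Simulation with 10,000 trials per setting, 58 per arm, difference 12, total SD 23.1, normal outcomes and two-sided alpha 0.05. Two inputs are assumed because the document does not give them: 35% of patients with 4-part fractures, and a difference in 24-month Constant score between 3- and 4-part fractures of 0, 10 or 20 points.

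| Assumed 3- vs 4-part difference | ANOVA with stratum | Kruskal-Wallis | van Elteren (stratified rank) | Kruskal-Wallis type I error |
|---|---|---|---|---|
| 0 | 80.1% | 78.4% | 77.8% | 4.7% |
| 10 | 80.8% | 77.8% | 78.6% | 4.8% |
| 20 | 85.9% | 78.6% | 83.6% | 3.1% |

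The first three result columns are power. The loss against the stratified ANOVA is 80.1 − 78.4 = 1.7, then 80.8 − 77.8 = 3.0, then 85.9 − 78.6 = 7.3 points. At a zero difference the loss comes from ranking alone. At 20 points most of it comes from dropping the stratum, since the stratified rank test recovers 83.6 − 78.6 = 5.0 points.

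Two limits apply. The outcomes were normal, whereas the fallback is meant for data that are not. Each test was run on its own, because the switch cannot be simulated without a stated trigger.

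**4. The GEE.** No arithmetic applies. Its sentence names an effect over time and lists the pre-operative score among the repeated measures. It stands under a primary objective that compares two treatments over two years. Both a time effect and a treatment effect over time fit the words.

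**The case against.** **The planned ANOVA is not an error.** Under 1:1 stratified randomisation, comparing 24-month means with the stratum included is unbiased and matches the sample size calculation. This stands. A reader might infer that leaving baseline out biases or invalidates the primary result, and the document does not support that.

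**The gain may be small.** Baseline is taken after an acute displaced fracture, the Constant score weights motion and strength, and IPAQ asks about the last seven days. Such scores may mostly reflect the injury. At r = 0.1 to 0.3 the gain is only 0.4 to 3.6 points. This also stands.

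**The article condenses a fuller plan.** Covariates of secondary models, trigger criteria and reporting format are often left to the analysis plan. This weakens any complaint about silence in the secondary ANOVAs. It does not remove the fallback point, because the article itself names an unstratified rank test as the replacement for the primary test. A mean difference could still be reported beside the rank test, but it would no longer be what the primary test assesses.

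**Stronger readings to avoid.**

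- That the Kruskal-Wallis test inflates type I error. In simulation it was at or below nominal.
- That the GEE tests time instead of treatment. It sits under a between-group objective, so a treatment effect over time is a natural reading.
- That counting baseline as one of five visits shrinks the treatment effect to four fifths. This needs a single constant effect across all visits, a model the document never specifies. With treatment-by-visit terms the 24-month contrast is not shrunk.
- That age must be a covariate. Nothing in the document requires it.

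**Conclusion.** The point holds as one of precision and specification. The primary analysis is valid, but it leaves unused a covariate already collected. The power gain is from 78.9% to between 79.3% and 89.1% for an assumed correlation of 0.1 to 0.5, with the lower part of that range plausible.

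The fallback is the weightier part. On an undefined, data-dependent condition it would replace a stratified comparison of means with an unstratified rank test that does not estimate the target quantity. Its power cost is about 2 to 7 points, depending on an assumed difference between fracture types and on normal outcomes, with no type I inflation seen for the test itself.

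The GEE wording is ambiguous and no more than that. The changes are worth making because they need no new data, but nothing here threatens the trial's validity.

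**What to change.** - **Primary analysis:** a linear model of the 24-month Constant score on treatment, fracture-type stratum and baseline Constant score, reporting the mean difference with its 95% CI.
- **If residuals are poor:** keep this model with robust or bootstrap inference. Use a stratified rank test (van Elteren) only as a sensitivity analysis, and delete the switch to Kruskal-Wallis.
- **ASES, EQ-5D-5L, PROMIS and IPAQ:** the same form, each with its own baseline and the stratum.
- **GEE:** state that it includes treatment-by-visit terms and reports the 24-month treatment contrast.

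The cost is a change of analysis wording, ideally made before outcome data are examined by arm. No new data, visits or patients are needed.

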### Randomization and blinding

Figure 1 shows the flow of procedures in the trial. Study group allocations will have been pre-determined from an online randomization generator and catalogued in sealed envelopes by personnel independent of the study. The allocation will be in a 1:1 ratio, stratified by fracture type (3 and 4 part): 3- and 4-part fractures will be stratified using permuted blocks of variable length (4 to 6). Randomization and allocation to treatment will be determined on the day of the first assessment in the plaster room clinic within 7 days post injury or at the time of the emergency room visit if the patient is unable to return home. The research coordinator will open the sealed envelope containing the study allocation and will inform the surgeon of the patient’s assigned treatment: non-operative or ORIF treatment. Patients assigned to the ORIF group will have surgery scheduled within 7 days following injury.

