### Primary outcome measures

#### Constant score [46]

The Constant score has been validated and normalized in comparison to disease free patients and places greater emphasis on range of motion and strength and has been adopted by the European shoulder society for functional assessment of the shoulder. The Constant Score records a variety of shoulder measurements including an objective test of strength using a spring-loaded measuring device and reflects an overall clinical functional assessment. This instrument is based on a 100-point scale.

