### Sub-analysis

In addition to the primary and secondary analyses outlined above, several other analyses are planned, though the study is not primarily powered for these statistical analyses. We will perform a subgroup analysis on the above outcome measures to assess whether there is a difference between 3- and 4- part proximal humerus fractures. This will primarily include a subgroup analysis of the Constant score, within groups of fracture type: 3- and 4- part fractures. The second will be a multivariable assessment of the progression of osteoarthritis between pre- and post-operative shoulders. A multivariable regression analysis will also be conducted of possible factors associated with progression of shoulder osteoarthritis, including demographic variables and fracture type. The third will be a multivariable regression analysis to determine which factors may be associated with functional outcome: with the Constant score as the dependent variable, demographic and radiographic factors (including osteoporosis) will be analyzed to determine if prognostic factors exist that may assist in planning treatment.

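### Pre-specifying age and sex in the primary Constant-score model would probably tighten the treatment estimate at almost no cost; their omission is not an error

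*Protocol article*

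**What the plan says.** Under Primary objective analysis, the article fixes both the method and its one covariate: "An ANOVA will be used to assess whether there is a statistically significant difference between treatment groups for the mean Constant scores at 2 years," and then "with stratification factor included". Randomization and blinding identifies that factor. "The allocation will be in a 1:1 ratio", in permuted blocks within fracture type, 3-part or 4-part. No other covariate is named for the primary comparison.

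The Sub-analysis section plans a separate multivariable regression in which, "with the Constant score as the dependent variable, demographic and radiographic factors (including osteoporosis) will be analyzed". Its stated aim is to find out whether prognostic factors exist, and the section says the trial is not primarily powered for these analyses. Age and sex are not named there.

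The description of the primary outcome says that the Constant score "places greater emphasis on range of motion and strength". The Participants section enrols men and women over 60, with no upper age limit.

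The sample size rests on two inputs: "The minimum clinically important difference for the Constant score is 12", and a spread given "with standard deviation of 23.1 from measurements in previous studies of similar patient populations". Nothing is taken off that SD for covariates.

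**The concern.** Any part of the outcome variation that age and sex explain stays in the error term of the primary model. A score that leans on measured motion and strength, in men and women over 60 with no age ceiling, could well vary with both. The protocol is willing to examine demographic factors against this score in an exploratory regression, but does not use them in the one comparison where they could sharpen the treatment estimate.

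Precision matters in this trial because the authors hypothesise no statistically significant difference in function. A null result will be read through its confidence interval, set against a minimum important difference of 12 points.

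This point is separate from adjustment for the baseline Constant score, which is taken after the fracture. Age and sex are unaffected by the injury.

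**Working it through.** **Inputs from the article.** Difference 12 points; SD 23.1; alpha 0.05 (two-sided, which reproduces the stated size); power 80%; 58 per arm, 116 in total; 129 after allowing for 5% crossover; 160 after allowing for 20% loss to follow-up.

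**Reproducing the plan's figures.**
- Per arm: 2 x [23.1 x (1.960 + 0.842) / 12]^2 = 58.2, against 58 stated.
- Crossover: 116 / 0.95^2 = 128.5, so 129, as stated.
- Loss to follow-up: 116 / 0.95^2 / 0.8 = 160.7, against 160 stated.

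The calculation therefore closes with no covariate adjustment. The planned 80% power does not depend on age and sex.

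**Inputs that are assumptions.**
- R2, the share of within-arm variance that age and sex explain beyond fracture type. The article gives no value, so a range of 2% to 20% is shown.
- 64 evaluable per arm: 160 x 0.8 / 2.
- 11.4 points: 12 x 0.95, the target difference diluted for 5% crossover under intention to treat. Results for the undiluted 12 points are shown beside it.

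**Formulas.**
- Unadjusted SE = 23.1 x sqrt(2/64) = 4.08.
- Adjusted SE = 4.08 x sqrt(1 - R2) x sqrt(1 + 2/123). The last term, 1.008, charges for the two extra parameters; 123 is 128 - 2 - 3.
- Power from the noncentral t distribution; half-width = 1.979 x SE.

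| R2 assumed | SE | Half-width of 95% CI | Power, 11.4 points | Power, 12 points |
|---|---|---|---|---|
| no age or sex in model | 4.08 | 8.1 | 79.1% | 83.0% |
| 2% | 4.08 | 8.1 | 79.3% | 83.2% |
| 5% | 4.01 | 7.9 | 80.5% | 84.3% |
| 10% | 3.91 | 7.7 | 82.5% | 86.2% |
| 15% | 3.80 | 7.5 | 84.6% | 88.0% |
| 20% | 3.68 | 7.3 | 86.7% | 89.9% |

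**Break-even.** Adjustment pays once (1 - R2) x (1 + 2/123) falls below 1, that is, once R2 exceeds about 1.6%. If R2 were zero, the adjusted SE would be 0.8% larger than the unadjusted one.

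**Equivalent sample size.** Before the charge for two parameters, 128 / (1 - R2) - 128 gives about 7 extra evaluable patients at R2 5%, 14 at 10% and 32 at 20%.

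**Alpha.** If the interim analysis takes place, the final test is at 0.049. That lowers each power by about 0.2 of a percentage point and leaves the comparison as it is.

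**The case against.** The strongest case against is that nothing here is wrong. Randomisation makes the comparison without age and sex unbiased, the stratification factor is in the model as the design requires, and the sample size was computed on the same footing. All of that stands. With the stated 12 points and 64 per arm, power is already 83.0% without covariates.

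It also stands that the gain rests on an unknown R2. Restricting entry to patients over 60 narrows the age range and makes a low value plausible. At 5% the gain is small: 1.4 percentage points of power (80.5 - 79.1) and about 0.1 of a point in half-width.

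Three stronger readings are tempting, and the article does not support them.
- A reader might infer that the protocol itself expects age and sex to predict the score. The Sub-analysis section speaks only of demographic factors and leaves open whether any prognostic factor exists. The prognostic expectations stated under Purpose and hypothesis concern Neer classification and initial displacement. The remark on what the Constant score emphasises does not mention age or sex.
- A reader might infer that chance imbalance in age or sex invalidates the primary estimate. It moves the estimate only as far as these variables predict the outcome. A one-SD imbalance in the prognostic score shifts it by sqrt(R2) x 4.08, or 0.9, 1.3 and 1.8 points at R2 5%, 10% and 20%. The unadjusted standard error already allows for this, so it is the same effect as the loss of precision and not a second one.
- A reader might infer that precision is certainly lost. At R2 of about 2% or less there is essentially nothing to gain.

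The statistical analysis plan is not at hand and may add adjusted analyses. The article does, however, name the primary model and its covariate, so the model is a stated choice and not a detail left open.

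**Conclusion.** This is an optional efficiency improvement, not a flaw in the plan. The primary ANOVA is valid as written and consistent with its sample size, but it probably gives a less precise treatment estimate than the same data could. Under the assumed R2 of 2% to 20%, with 64 per arm and SD 23.1, the gain in power runs from 0.2 to 7.6 percentage points for 11.4 points (79.1% to 79.3-86.7%), and from 0.2 to 6.9 for the stated 12 points (83.0% to 83.2-89.9%). The half-width changes by between nothing and 0.8 of a point. The size of the gain rests wholly on R2, which the article does not supply. The direction is safer ground: from nil to modest, with no material harm if R2 is near zero.

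**What to change.** Before any outcome data are seen, specify the primary analysis as a linear model for the 24-month Constant score with treatment, fracture type, age as a continuous variable, and sex. Report the model with treatment and fracture type alone as a sensitivity analysis.

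The cost is one line of wording and two degrees of freedom out of about 125. No new data are needed and the sample size need not change. If age and sex explain about 2% of the variance or less, the change buys essentially nothing. The gain is also lost if the Kruskal-Wallis fallback is used, because that test takes no covariates.
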